### Participants

Study participants (*n* = 120 completers) are clients and their partners recruited from the Monash Healthy Sleep Clinic (Melbourne, Australia) and the community via advertisement, e.g. radio, newspaper, flyer drops, and social media. Our estimated recruitment numbers shown in Fig. 1 are based on a 4:1 referral-to-screening ratio, and our initial screening visit goal assumes a 20% screen failure rate. Our randomisation numbers assume 20% attrition. These rates are similar to those we have experienced in other similar insomnia trials.

### Inclusion and exclusion criteria

Participant eligibility criteria are outlined in Table 1. We considered carefully whether to exclude participants taking sleep medications but decided against this based on the recommendations of Morin et al. [42]. We are, however, tracking medications throughout the study.

**Table 1 Tab1:** Eligibility criteria for participants

Inclusion	Exclusion
a) Adults (> 18 years of age) b) Diagnosis of insomnia disorder, per DSM-5 c) A stable bed partner willing to participate in the study (i.e. someone with whom the client has lived and shared a bed ≥ 5 nights/week for ≥ 1 month d) Fluent in English	a) Unmanaged psychosis or manic episodes in the past 2 months in either partner b) Untreated sleep disorders other than insomnia (managed sleep disorders such as obstructive sleep apnoea treated with continuous positive airway pressure will be allowed) c) Current substance-use disorder (SUD), or SUD within the last 90 days d) Current or history of domestic violence e) Shift work f) Travel across time zones in the past month prior to commencing treatment g) Pregnancy after the first trimester h) An infant < 1 year of age

There are no exclusion criteria related specifically to the partner, other than exclusions a, c, d, and h

We considered carefully whether to exclude participants taking sleep medications, but decided against this based on the recommendations of Morin et al. [42]. We will, however, track medications throughout the study

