#### Allocation to treatment conditions

Participants are randomised to one of three treatment conditions. Randomisation occurs within clinicians such that each clinician sees an equal number of clients in each treatment condition. Randomisation occurs separately for male and female clients to help ensure equal male:female ratios for each treatment condition.

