#### Power considerations

We have powered the study for Hypothesis 1A. Hypotheses 1A tests the outcome (i.e. adherence) related to what makes PA-CBTI unique from traditional CBTI. Given the relatively small sample size of our pilot PA-CBTI data (unpublished), we have benchmarked our power analysis to find a medium effect (Cohen’s f = 0.25) in a 3 × 5 (group × session) multivariate analysis of variance (MANOVA) (five sessions, as there are no adherence data in weeks 1 or 2). With alpha = 0.05 and a two-tailed test, a sample size of 120 (40 per group) provides a power of 0.81 to detect a significant effect. Follow-up comparisons also have adequate power [55].

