#### Statistical tests of hypotheses

##### Aim 1

Hypothesis 1A predicts that individuals under partner-assisted conditions will show greater adherence and lower attrition than those under the individual treatment condition. We will test this with 3 × 5 (group × session) MANOVA. The MANOVA will first test the entire set of adherence variables by constructing a latent variable of adherence and using this as the outcome variable. If significant, we will then examine the univariate results for each specific adherence measure. Significant main effects of group (the hypothesised effect) will be followed by comparing PA-CBTI with each of the other groups. Hypothesis 1B will use the Chi-squared test to test the proportion of participants who complete each treatment, with similar follow-ups.

##### Aim 2

Hypothesis 2A anticipates that greater adherence will relate to better sleep outcomes in PA-CBTI and i-CBTI, but not PA-SMT. Multiple regressions will test the hypothesis, with explanatory variables of group (dummy coded), adherence (in the last week of treatment), and group × adherence interaction. The outcome variable will be diary-derived sleep efficiency in the last week of treatment. The interaction term is the effect of interest. Follow-ups will examine the adherence effect within each group. Hypothesis 2B will be tested with Sobel mediation. We hypothesise that PA-CBTI will show (via sleep diaries) greater mean daily sleep efficiency at post-treatment and 6-month follow-up compared with i-CBTI. This effect will be mediated by adherence at the end of treatment (adherence cannot be measured at follow-up since we will not be prescribing sleep schedules).

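### Pre-treatment sleep-medication use is left out of the Hypothesis 2A and 2B analyses, so the non-randomised adherence-to-sleep slopes can be confounded by it (minor)

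*Protocol article*

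**What the plan says.** Under Inclusion and exclusion criteria, the article states: "We considered carefully whether to exclude participants taking sleep medications but decided against this". Table 1 sets no condition that use be stable. The article then adds: "We are, however, tracking medications throughout the study".

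Under Statistical tests of hypotheses (Aim 2), Hypothesis 2A is tested by multiple regression "with explanatory variables of group (dummy coded), adherence (in the last week of treatment), and group × adherence interaction". On the outcome it says: "The outcome variable will be diary-derived sleep efficiency in the last week of treatment". The interaction is named as the effect of interest, and follow-ups then look at the adherence effect inside each group.

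For the second hypothesis: "Hypothesis 2B will be tested with Sobel mediation". PA-CBTI is expected to show higher mean sleep efficiency than i-CBTI at post-treatment and at 6 months, and: "This effect will be mediated by adherence at the end of treatment".

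Medication appears in neither analysis, nor among the examples under Exploratory analyses.

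**The concern.** Only the arms are randomised. How well a client adheres is not, so any slope of sleep efficiency on adherence is observational, both in the 2A follow-ups and in the mediator-to-outcome step of 2B.

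Sleep medication is a plausible common cause. Under Sleep diaries, stimulus-control adherence is built from the share of wake time spent out of bed, and the sleep-restriction score counts naps. A drug that changes night-time wakefulness or daytime sleepiness can therefore move the adherence score. It can also move sleep efficiency, which in 2A comes from the same diary in the same week.

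Aim 2 is worded to support the reading that adherence drives better sleep. If part of the slope reflects who was taking medication at entry, that reading is weakened, although the article says medication is being tracked.

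**Working it through.** The article states no figure for this point, so there is none to reproduce. Its power calculation concerns Hypothesis 1A and is not involved. Medication prevalence and effects are not given either; the values below are assumptions, shown as a range.

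**Inputs.** p = proportion using sleep medication before treatment, 0.3 to 0.5 (assumed). a = shift in adherence and b = shift in sleep efficiency between users and non-users, in residual SD units, with a = b = 0.4 to 0.6 (assumed). 40 clients per arm (Power considerations). True adherence effect set to zero.

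**Step 1: spurious correlation within a group.** With a = b, r = p(1−p)ab / [1 + p(1−p)a²].
- p = 0.3, a = b = 0.4: 0.21 × 0.16 / (1 + 0.21 × 0.16) = 0.0336 / 1.0336 = 0.033
- p = 0.3, a = b = 0.6: 0.0756 / 1.0756 = 0.070
- p = 0.5, a = b = 0.4: 0.0400 / 1.0400 = 0.038
- p = 0.5, a = b = 0.6: 0.0900 / 1.0900 = 0.083

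If medication moves adherence and sleep efficiency in opposite directions, ab is negative and the same values carry a minus sign.

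**Step 2: size against sampling error.** At n = 40 the standard error of a null correlation is about 1/√39 = 0.16, so the bias is at most about half a standard error (0.083 / 0.16 = 0.52). In simulation of a single-arm follow-up with these inputs, the false-positive rate was 0.051 to 0.084 against a nominal 0.05. With larger assumed shifts of 0.8 SD each and p = 0.35 it reached about 0.12.

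**Step 3: Hypothesis 2A interaction.** Adherence to sleep restriction and stimulus control is calculated in all three arms. If medication acts alike in each, it adds the same amount to each slope and drops out of the differences between slopes. Simulating the regression as described, with 40 per arm and the same inputs, gave an interaction false-positive rate of 0.048 to 0.051, that is, no inflation.

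**Step 4: Hypothesis 2B.** The group-to-adherence step is protected by randomisation. The adherence-to-sleep step is not, and an error in its slope enters the indirect effect multiplied by the group effect on adherence. With both CBTI arms together (n = 80), shifts of 0.5 SD each and p = 0.35 to 0.5, the false-positive rate for that slope was about 0.08.

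**Step 5: the randomised comparison.** For PA-CBTI against i-CBTI, with p = 0.35 or 0.5 and a medication effect of 0.5 SD on sleep, the simulated mean bias was essentially zero and the type I error 0.049 to 0.051. Chance imbalance in baseline use has an SD of √[2p(1−p)/40] = 0.102 (p = 0.3) to 0.112 (p = 0.5), which is ordinary random error that the test already allows for.

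**The case against.** The strongest reply is that 2A rests on the interaction, and confounding that is similar across arms cancels from it. This stands: nothing in the article suggests that medication confounds adherence differently by arm. It leaves the within-group follow-ups and the 2B path exposed.

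A second reply is that a condensed article may leave covariates to the analysis plan, and that the listed terms are not said to be exhaustive. This stands in part. The article does spell out the 2A terms, and tracking is the only response to medication use that it describes. It remains a reason to grade the point low.

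Third, the direction is not known. If users keep to the sleep window less well yet sleep better, the bias works against the hypothesis. This stands, and no direction is claimed here.

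A reader might also infer that the 6-month contrast is confounded by medication. The documents do not support that. The arms are randomised ("Randomisation occurs within clinicians such that each clinician sees an equal number of clients in each treatment condition"), so baseline use cannot bias the contrast systematically. Use begun or changed after randomisation is an intercurrent event: it bears on what the contrast means, and its handling is commonly left to the analysis plan. In a trial described as an effectiveness trial, sleep under whatever care clients use is a legitimate target.

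Nor should medication be called unrestricted. Table 1 excludes current or recent substance-use disorder, and the decision to admit users is presented as a considered choice resting on a cited recommendation.

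**Conclusion.** The point holds in a narrow form. The within-group adherence slopes of Hypothesis 2A and the adherence-to-sleep-efficiency path of Hypothesis 2B are open to confounding by pre-treatment medication use, which the described analyses ignore.

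The spurious correlation is about 0.03 to 0.08 in absolute value, of unknown sign. It rests on assumed prevalence (30-50%) and assumed shifts (0.4-0.6 SD), since the article supplies neither. The 2A interaction is unaffected unless the confounding differs by arm. The 6-month randomised contrast is not confounded. Hypothesis 1A, for which the trial is powered, is untouched.

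Severity is minor: the hypotheses are secondary and the bias is modest under moderate assumptions.

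**What to change.** Add pre-treatment sleep-medication use (yes/no) as a covariate in the Hypothesis 2A regression, in its within-group follow-ups, and in both the mediator model and the outcome model of Hypothesis 2B.

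Do not adjust for medication use recorded after randomisation, including during treatment. Such use may be a consequence of the assigned arm, and conditioning on it could introduce bias.

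Optionally, report medication use by arm at 6 months beside sleep efficiency, as an aid to interpreting the contrast.

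The cost is one degree of freedom per model. The sample size does not change, and no new data are needed provided the medication tracking covers the pre-treatment assessment.

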### Screening and eligibility

When participants first express interest in the study, they complete a brief pre-screening questionnaire either online or via telephone. This questionnaire is administered to both clients and partners and asks questions pertaining to sleep, mental health, time travel, shift work, and relationship status.

At the initial visit, and following written informed consent, a 2- to 3-h study eligibility screening and pre-treatment assessment is conducted. This assessment involves: (a) Duke Structured Interview for Sleep Disorders (DUKE; [39]) to assess insomnia and other potential sleep disorders (client only); (b) Structured Clinical Interview for DSM-5 (SCID-5; [40]) to document any other psychiatric disorders (client only); (c) medical and sleep history; and (d) a series of self-report measures as shown in Table 2. Participants also undergo an overnight polysomnography to rule out excluded sleep disorders.

### Study intervention

Following pre-treatment assessments, couples are randomised to one of three interventions: PA-CBTI, i-CBTI, or PA-SMT. All three interventions consist of seven weekly, 1-h sessions. Participants can discontinue the treatment or the study at any stage. If one of the members of the couples wishes to withdraw, they must withdraw as a couple. Post-treatment and 6-month follow-up data will be collected for those who discontinue the treatment unless they withdraw from the study.

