**Methods:**

This study is a mixed-effects randomised effectiveness trial of partner-assisted CBTI (PA-CBTI). It is an “effectiveness” (as opposed to “efficacy”) trial, due to the focus on “real world” clinic-based clients and adherence/attrition as outcomes. Participants will include 120 clients with insomnia who are randomly assigned, in equal numbers, to PA-CBTI, traditional individual CBTI (i-CBTI), or partner-assisted sleep management therapy (PA-SMT; which serves as the control group). All interventions consist of seven weekly 1-h sessions. Treatment outcome is evaluated using clinician-rated treatment adherence, and diary-based adherence to stimulus control and sleep restriction. Clients and partners complete major assessments at pre- and post-treatment, and at 6-month follow-up. Secondary outcome variables include actigraphy, self-report measures related to sleep, comorbid psychopathology, and relationship functioning.

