#### Cognitive behavioural therapy for insomnia (CBTI) and partner-assisted CBTI (PA-CBTI)

We employ a CBTI protocol based on those recommended by the leading experts in the field [40, 41]. This protocol covers the four-factor model of insomnia, sleep restriction, stimulus control, sleep hygiene, stress and relaxation, cognitions and sleep, and relapse prevention. PA-CBTI follows the same session outline as CBTI. The “partner-assisted” aspect involves: (a) teaching the partner all of the same concepts and psychoeducation as provided to the client; (b) providing handouts of session material tailored specifically for the partner; (b) actively engaging the partner in all treatment-related decision making and problem-solving; and (d) actively engaging the partner in determining how they can assist the client to implement treatment recommendations at home and assigning those behaviours as the partner’s homework. For example, we engage the partner along with the client in reviewing sleep diaries of the client, identifying patterns, deciding on changes to make, and determining whether/how to titrate time-in-bed for the coming week. The partner also actively assists the client to pick bed/wake times, activities and locations related to stimulus control principles, and strategies for staying awake and/or avoiding naps, etc. In essence, anything a client does in traditional CBTI is done with input from the partner in PA-CBTI. The therapist emphasises empowerment of the partner to provide support and structure for the client at home to maximise adherence to the intervention.

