### Outcome measures

#### Primary outcome measures

Assessments include: (a) major assessments conducted pre- and post-treatment and at 6-month follow-up for both the client and partner; and (b) weekly and daily assessments for the client as shown in Table 2.

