##### Client adherence form (CAF)

The CAF was created for the US Veterans Affairs CBTI training program using an expert consensus process. Using a scale of 1 to 6 (no adherence to complete adherence) or not applicable (for strategies not yet taught), therapists rate client adherence on six specific CBTI activities [22]. A modified version has been developed for this trial, including for PA-SMT. Clinicians complete this form after each treatment session every week.

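### The joint-withdrawal rule ends post-treatment and 6-month data collection from a willing client when only the partner leaves the study

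*Protocol article*

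**What the plan says.** Three consecutive sentences under Study intervention set the rules for stopping.

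- Two levels of stopping are recognised: "Participants can discontinue the treatment or the study at any stage".
- Withdrawal is joint, with no exception by arm or by which member leaves: "If one of the members of the couples wishes to withdraw, they must withdraw as a couple".
- Later data depend on which level applies: "Post-treatment and 6-month follow-up data will be collected for those who discontinue the treatment unless they withdraw from the study".

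Primary outcome measures describes major assessments of both members at pre-treatment, post-treatment and 6 months, and separately "weekly and daily assessments for the client as shown in Table 2". Statistical tests of hypotheses bases Hypothesis 2B on the client's diary sleep efficiency at post-treatment and 6 months, PA-CBTI against i-CBTI. Among the secondary measures, the abstract says: "Secondary outcome variables include actigraphy, self-report measures related to sleep, comorbid psychopathology, and relationship functioning".

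On losses, Participants says only this: "Our randomisation numbers assume 20% attrition". It gives no split by which member of the couple leaves.

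**The concern.** The trial seeks to learn what happens to the client's adherence and sleep. A rule that lets one person's decision end data collection from another, who still consents, creates missing data that could be avoided. Recording the reasons for attrition, as Attrition analysis provides, describes such a loss but cannot recover data never collected.

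The partner's own assessment load makes a partner-only exit conceivable in any arm: Limitations lists the ISI, diary and actigraphy for partners at each assessment point. What is at stake is mainly the 6-month comparison of sleep efficiency in Hypothesis 2B and the client's other follow-up outcomes.

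**Working it through.** No published figure is in dispute, so the check is a reading of the text, with a short calculation to see whether the loss can be sized.

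**Step 1: what the rule covers.** The rule sentence does not say whether withdrawal is from treatment or from the study. The sentence after it uses *discontinue* for treatment and *withdraw* for the study. There are two readings:

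| Reading of the rule | Partner alone leaves | Client's post-treatment and 6-month data |
|---|---|---|
| Withdrawal from the study (natural reading) | Client must leave the study too | Not collected |
| Withdrawal from treatment only | Client must stop treatment | Still collected, under the following sentence |

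The concern holds on the first reading. On the second, follow-up is kept and only the wording needs clarifying.

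**Step 2: which client data depend on the partner.**

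| Client data | Source | Partner needed? |
|---|---|---|
| Diary sleep efficiency, post-treatment and 6 months | Client's diary | No |
| ISI | Client's self-report | No |
| Dyadic analyses of sleep | Both members | Yes |

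Diary adherence and the therapist's rating also concern the client alone ("therapists rate client adherence on six specific CBTI activities"). They are collected in treatment, at sessions 3 to 7 for the adherence measures, so they depend on whether treatment continues. That is a separate question, taken up under the objection.

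**Step 3: what is lost, by timing of the partner's exit.**

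- After session 7: completion and adherence are already recorded. What remains to be lost is the client's later data, chiefly 6-month sleep efficiency for Hypothesis 2B. Keeping the client in follow-up recovers it.
- Before session 7, with treatment stopping: post-treatment and 6-month data are both lost. Keeping the client in follow-up recovers the sleep outcomes but not end-of-treatment adherence, the mediator in Hypothesis 2B. The plan already intends to collect these outcomes from clients who stop treatment, so no new procedure is needed.

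**Step 4: can the size be derived?** The inputs are 120 completers and 20% attrition (Participants), in three equal arms.

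- Randomised: 120 / (1 − 0.20) = 150, or 150 / 3 = 50 per arm.
- Lost: 150 − 120 = 30, or 10 per arm.

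The article does not say how many of the 10 per arm, if any, would be partner-only exits with a willing client. Nor is 120 / 3 = 40 per arm the expected number with 6-month data: it counts completers, and the plan also follows people who stop treatment. A change in power or detectable difference would therefore need both an invented count and a follow-up denominator that the article does not give.

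**The case against.** The case for the rule is reasonable. Couples are what is randomised, and Table 1 makes a willing partner an entry criterion. Relationship functioning is a named secondary outcome and dyadic analyses are listed as exploratory, so complete dyads have value. One rule for all arms treats a partner exit alike in the arms compared under Hypothesis 1B. Reasons for attrition are already recorded and differential attrition is to be examined.

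Most of this stands, but it explains why couples enter together. It does not require ending follow-up of a client who still consents. Keeping that follow-up in every arm also preserves equal handling.

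A reader might go further on i-CBTI. Partner input is what the assisted version adds ("anything a client does in traditional CBTI is done with input from the partner in PA-CBTI"), so a partner's exit seems to stop a therapy in which the partner has no role. A reader might infer that this lowers i-CBTI completion and favours Hypothesis 1B, and that i-CBTI clients should be allowed to finish. The document does not support that inference, for three reasons:

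- The rule applies in all arms, so forced exits can occur in the partner-assisted arms too. The net effect on the contrast could go either way.
- The article does not define completion, so how such a client would be counted is itself an inference.
- Continuing treatment only in i-CBTI would make a partner exit end treatment in some arms and not in another. That would affect the 1B comparison and select the session 3 to 7 adherence data for 1A and 2A differently by arm.

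Nor does the article give a reason for the rule, so it cannot be said that its purpose is to keep dyads complete.

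**Conclusion.** The point holds for follow-up, as a minor matter. On the natural reading, a partner-only exit from the study needlessly ends collection of the client's post-treatment and 6-month data, in any arm.

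This rests on two assumptions: that the rule refers to leaving the study, and that at least some clients would be willing to continue when their partner is not. Neither the number of such clients nor the direction of any bias can be derived from the article. The number may be zero and the effect small. No loss of power, and no bias in the completion comparison, is claimed.

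**What to change.** Reword the rule under Study intervention so that, in all three arms, when only the partner withdraws from the study:

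1. partner data collection stops;
2. the client's post-treatment and 6-month data continue to be collected unless the client also withdraws;
3. the attrition record shows which member initiated the withdrawal, and this is reported by arm beside the Hypothesis 1B completion result.

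Whether treatment continues after a partner exit stays as the protocol has it.

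The cost is a wording amendment to protocol and consent, and one extra field on the attrition record. Some dyads will be incomplete in the relationship analyses (secondary) and the dyadic analyses (exploratory). Trial status expected enrolment to continue until July 2019, so the change can help only couples who have not already withdrawn. For earlier withdrawals, who initiated them can be reported where the existing attrition records allow.
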